#### Recruitment

In order to recruit HCP with diverse socio-demographic characteristics, occupational responsibilities, and influenza vaccination histories, eligible HCP were invited to participate using a stratified sampling strategy that targeted eligible participants in groups (strata) categorized by sex, age, occupation, and previous year influenza vaccination status. This systematic approach was intended to minimize convenience sampling, which can introduce both known and unknown biases. Each group includes individuals with unique characteristics known to potentially affect influenza vaccine immunogenicity and effectiveness.

At CHS, a list of eligible HCP at each facility was generated and categorized into groups based on age (18–34, 35–49, ≥50 years old), sex, occupational categories (1- Physicians; 2 - Nurses, medical therapists, and professional technicians; and 3 - Medical assistants and support staff), and prior season influenza vaccination status (yes vs. no). Thus, prior to each year of the study, the sample is drawn from 36 unique strata (2 sexes * 3 age groups * 3 occupation groups * 2 prior season vaccination status groups). This stratified sampling strategy will be applied to potential new participants each year.

At each hospital, goals are set for the minimum and maximum number of enrollees per strata; then, recruitment is implemented in three waves. During the first wave of recruitment, HCP from the 36 strata are invited at random to participate in the study. Next, in Wave 2, we identify study strata where additional recruitment is needed and expand direct invitations to additional HCP who have not yet been invited to join the study. In strata where all HCP have been contacted but recruitment goals have not been met, we will recruit similar HCP, prioritizing HCP who are similar in previous vaccination status, followed by age, sex, and lastly by profession. Finally, in Wave 3, we accept volunteers to meet the total sample goals for each facility. All potential enrollees will be recorded in a recruitment log in order to track invitations, acceptance, and refusal and reasons for refusal.

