#### Molecular diagnostics

Specimens from Beilinson Hospital are stored at 4 °C and delivered by courier to the Clinical Virology Laboratory (CVL) at Soroka University Medical Center twice a week, where they are immediately aliquoted and frozen at − 80 °C. Specimens from participating Soroka University Medical Center HCP are brought to the laboratory daily, where they are aliquoted and frozen.

After one freeze-thaw cycle, specimens are tested for influenza A viruses [A(H1N1)pdm09 and A(H3N2)], influenza B viruses, respiratory syncytial virus (RSV), human metapneumovirus, and coronaviruses (NL63, 229E, OC43, HKU1) using validated multiplex quantitative real-time reverse transcription polymerase chain reaction (mqRT-PCR) assays [32], with protocols, primers, probes, and reagents supplied by Hy-labs (Israel) and Integrated DNA Technologies (USA). The CVL, in collaboration with the University of Michigan (Ann Arbor, Michigan, US), has completed the World Health Organization and US CDC influenza proficiency panels. Quality Control for Molecular Diagnostics (Glasgow, Scotland, UK) proficiency panels were also completed for influenza, RSV, human metapneumovirus (hMPV) and coronaviruses.

Some specimens will have molecular characterization with genetic sequencing and other assays to detect genetic markers to determine viral subclades and antiviral resistance at a reference laboratory approved by the study steering committee. Remaining aliquots of all study specimens may be sent to a US CDC-designated facility (also approved by the study steering committee) for additional virus characterization, banking, and storage. No specimens will contain personal identifiers.

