#### Data analysis of VE

Rates of acute illness associated with mqRT-PCR confirmed influenza virus infection (influenza illness) will be calculated as the number of influenza illnesses divided by person-time measured in weeks of active surveillance. Regression models will be used to estimate influenza vaccine effectiveness (1 – rate of influenza illness among vaccinated HCP/rate among unvaccinated HCP * 100) with 95% confidence intervals. Adjusted models of influenza vaccine effectiveness will include study year, calendar time (i.e., weeks between illness onset and week of peak of influenza season), and a propensity for vaccination score calculated using multivariable logistic regression [40]. Other potential confounders, including study site, will be examined and included in the adjusted model if they change IVE point estimates by > 5%.

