### Strengths

Our study benefits from the fact that all enrolled HCP are members of CHS, and therefore extensive information is recorded in the EMR, which provides real-time data about ambulatory visits, hospitalizations, and medication use. In addition, the EMR provides reliable historic data about the participants, such as prior vaccination information, socio-economic variables, and data about health status and health behaviors. In our study, even if an ARFI is not reported through the SMS surveillance system, daily monitoring of the EMR for medical visits and medications will allow us to identify illnesses and contact participants directly in order to collect respiratory specimens and complete the illness survey. Combining our study with EMR data and data from the two hospitals’ human resources departments will also allow us to reliably map the impact of illness on missed work and to evaluate days worked when ill (presenteeism).

In addition, the broad case definition of an ARFI promises to be more sensitive for influenza illness than case definitions used in previous HCP research [24] and should allow us to characterize a continuum of mild to moderately severe illnesses. Another strength is that the two study sites (Soroka University Medical Center and Beilinson Hospital) are among the largest hospitals in Israel, and the populations they serve and the HCP they employ vary in socio-demographic and economic characteristics. Soroka University Medical Center, the only general hospital in the Negev region in southern Israel, serves two main local populations: Jews, who mostly live in urban settings, and Bedouin Arabs, who live in a range of settlement types, from cities to unrecognized rural villages that lack electricity and running water [42, 43]. Beilinson Hospital, located in central Israel, serves a mostly urban population of a relatively higher socio-economic status compared to Soroka University Medical Center. Conducting our study in these two different settings may allow us to identify socio-demographic differences in KAP, vaccine uptake, and influenza illness attack rates. The use of mixed methods, including laboratory, clinical and epidemiological quantitative data, and in-depth qualitative interviews, creates a comprehensive approach, which is particularly important when trying to understand issues of influenza vaccine compliance and hesitancy. Finally, the study cohort includes several unique sub-studies.

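### Study site enters the VE model only if it moves the IVE estimate by more than 5%, a cut-off of unstated scale whose tolerance for confounding changes with the VE observed

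*Protocol article*

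**What the plan says.** In the protocol article, Data analysis of VE defines effectiveness through the rate ratio: "1 – rate of influenza illness among vaccinated HCP/rate among unvaccinated HCP * 100". It then lists what is always in the model: "Adjusted models of influenza vaccine effectiveness will include study year, calendar time" and a propensity score for vaccination. Site is handled differently: it is named among the other candidate confounders, which are to be "included in the adjusted model if they change IVE point estimates by > 5" per cent. The section does not say whether that is a relative change or a change in percentage points.

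Two other sections bear on site. Under Recruitment: "At each hospital, goals are set for the minimum and maximum number of enrollees per strata", with prior-season vaccination status as one of the stratifying factors. Under Strengths, after describing how the populations of the two hospitals differ: "Conducting our study in these two different settings may allow us to identify socio-demographic differences in KAP, vaccine uptake, and influenza illness attack rates".

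**The concern.** Site confounds the vaccine comparison if the hospitals differ both in coverage and in influenza risk. The article names both as differences that the two settings may show, and it recruits to separate goals in each hospital. Such a factor would normally be fixed in the model in advance. Here its inclusion waits on a screen applied to the estimate itself.

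The screen is also on an awkward scale. Confounding acts multiplicatively on the rate ratio, while the rule looks at 1 minus the rate ratio. A given amount of site confounding therefore produces a different change in IVE at each level of VE. What is at stake is a site bias that could have been removed cheaply, and a model whose content depends on the result.

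**Working it through.** **The plan's own figures.** Cohort size gives 2340 participants, 40% coverage, a 10% attack rate and VE 50%. That is 936 vaccinated and 1404 unvaccinated.
- 10% read as the overall rate: the unvaccinated rate is 0.10/(0.6 + 0.4 × 0.5) = 12.5%, giving 58.5 and 175.5 events (234 in all). SE of the log rate ratio = √(1/58.5 + 1/175.5) = 0.151, so the 95% CI for VE is 33% to 63%.
- 10% read as the unvaccinated rate: 46.8 and 140.4 events (187 in all), 95% CI 30% to 64%.

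The statement that the interval excludes zero is confirmed. These intervals are the yardstick for the bias below. The 5% cut-off is a chosen rule, so there is no derivation to reproduce.

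**What the cut-off tolerates.** With RR = 1 − VE, the rate-ratio shift that just meets the cut-off is 0.05 × VE/(1 − VE) on the relative reading and 0.05/(1 − VE) on the percentage-point reading.

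| VE | Relative reading | Percentage-point reading |
|---|---|---|
| 10% | 0.6% | 5.6% |
| 20% | 1.25% | 6.25% |
| 50% | 5.0% | 10% |
| 70% | 11.7% | 16.7% |
| 80% | 20% | 25% |

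**A worked example.** The article gives no coverage or attack rate by site, so these are assumptions: two equal hospitals, coverage 45% and 35%, unvaccinated attack rates 13% and 9%, true RR 0.5 in each.
- Vaccinated: (0.45 × 0.13 × 0.5 + 0.35 × 0.09 × 0.5)/0.80 = 0.045/0.80 = 5.625%.
- Unvaccinated: (0.55 × 0.13 + 0.65 × 0.09)/1.20 = 0.130/1.20 = 10.83%.
- RR = 0.519, so VE = 48.1%. The bias factor on RR is 0.519/0.5 = 1.038.

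The change is 1.9 points, or 1.9/50 = 3.8% relative. It is below 5 on either reading, so site is dropped.

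**The same confounding at other VE values.** Holding the factor at 1.038, the change in IVE is 0.038 × (1 − VE).

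| True VE | Without site | Change, points | Change, relative | Site enters (relative reading)? |
|---|---|---|---|---|
| 10% | 6.5% | 3.5 | 35% | yes |
| 30% | 27.3% | 2.7 | 9.0% | yes |
| 50% | 48.1% | 1.9 | 3.8% | no |
| 70% | 68.8% | 1.2 | 1.6% | no |

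On the percentage-point reading this example never enters. Stronger confounding shows the same dependence there. With coverage 50% and 30% and an attack-rate ratio of 1.5, the bias factor is (1.05/0.80)/(1.45/1.20) = 1.086. The change is then 7.8 points at VE 10% and 6.0 at VE 30% (site enters), but 4.3 at VE 50% (site does not).

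**With sampling error.** A Poisson simulation used 2340 participants, a 10% overall attack rate, equal hospitals, site as the only covariate and 3000 runs per case. Coverage was 45% and 35% with an attack-rate ratio of 1.5, a 4.2% bias in RR at every VE. On the relative reading, site was selected in 99%, 97%, 89%, 37% and 0.3% of runs at VE 10%, 20%, 30%, 50% and 70%. With the same coverage but no site difference in attack rate, it was still selected in 61% of runs at VE 10% and 0.6% at VE 50%.

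**The case against.** Change-in-estimate selection is a recognised approach, and the article does commit to examining site. On the relative reading the rule limits what one omitted covariate can leave behind to 2.5 points at VE 50%, and it is stricter at low VE. A bias of 1.9 points is small beside an interval of 33% to 63%. The article is also a condensed account and does not list the propensity-score covariates. If site or its close correlates are in the score, less confounding remains. All of this stands and limits the size of the point. Listing site among the other potential confounders does, however, suggest that it is not in the score.

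Four stronger inferences are tempting and are not supported:
- **That site is a known confounder by the authors' own account.** The Strengths section says the settings "may allow us to identify socio-demographic differences in KAP, vaccine uptake, and influenza illness attack rates". That is a possibility. Recruitment goals set per hospital do not by themselves link site to both uptake and risk.
- **That the confidence interval is invalid because it ignores the selection.** In the simulations, coverage of the 95% interval after selection stayed between 0.94 and 0.96.
- **That specimen handling biases detection by site.** Beilinson swabs are "delivered by courier to the Clinical Virology Laboratory (CVL) at Soroka University Medical Center twice a week", while Soroka swabs arrive daily, but nothing in the article indicates lost detection. Lower sensitivity at one site, unrelated to vaccination, would leave the within-site rate ratio unchanged. It would matter only if coverage also differed by site.
- **That the rule breaks down at VE 0.** That is true only on the relative reading, which the article does not specify.

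**Conclusion.** The point holds as a weakness in how the rule is fixed. Adjustment for site is left to a cut-off whose scale is unstated and whose tolerance on the rate ratio moves with the VE, so identical site confounding can be removed in one result and retained in another. Neither feature depends on assumed inputs.

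The size of the resulting bias does depend on them. It is 1.9 points at a true VE of 50% in the worked example, and about 0.5 to 7 points at that VE across the coverage contrasts (42% vs 38% up to 50% vs 30%) and attack-rate ratios (1.25 to 2.0) tried. The rule would retain only those of these biases that fall below its cut-off. The calculations assume equal-sized hospitals and a propensity score that does not already carry site. This is a modest, avoidable bias that should be corrected; a large bias has not been demonstrated.

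**What to change.** Move study site into the list of terms always included: a fixed site term, or a baseline rate stratified by site, in every adjusted VE model. The fixed term costs one degree of freedom against about 187 to 234 expected events, and needs no new data. With site always included, simulated coverage of the 95% interval was 0.947 to 0.954.

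For any remaining candidate confounders, state the criterion as a fixed relative change in the rate ratio, for example a ratio of adjusted to unadjusted RR that differs from 1 by more than 5%. This equals the relative reading of the present rule at VE 50% and stays the same at every other VE.

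A percentage change in the log rate ratio would not solve the problem. A 10% change on that scale corresponds to a rate-ratio shift of 1.1% at VE 10%, 7.2% at VE 50% and 17.5% at VE 80%, and it is undefined at VE 0. The whole change is a sentence or two in Data analysis of VE.

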#### Data analysis of immunogenicity

Since distributions of HI titer data are typically highly left-skewed, all statistical analyses will be conducted using log base-2 transformed titer data; results are then back-transformed to the original scale for ease of interpretation [28, 41]. Pre- and post-vaccine draws are assumed to be correlated within each person, thus repeated measures linear mixed models will be fitted to estimate geometric mean titers (GMT) and geometric mean ratios (GMR). Compound symmetric covariance error structures will be assumed for repeated measures within individuals. GMT will be calculated by back-transforming the least squares mean estimates of logged titer data. GMR will be calculated by back-transforming the difference of least squares means of post-vaccination and pre-vaccination logged titer estimates. GMR will be interpreted as the geometric mean fold ratio of post-vaccination titer to pre-vaccination titer. Multivariate estimates adjusted a priori for age and sex. Linear, quadractic, and cubic terms for age will be examined to consider possible nonlinear associations with age. Other covariates (e.g., education, household size, working in a hospital setting) may also be adjusted within multivariable models if they were associated with the number of prior vaccinations and either preseason GMT or post-vaccination GMR among vaccines.

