#### Timeline of enrollment

A total cohort of 2000 HCP will be enrolled over a three-year period. Enrollment periods are targeted prior to influenza seasons. During Year 1 of the study, which targeted the 2016/2017 influenza season, enrollment could not begin until October 6, 2016 due to funding and institutional approval delays. Recruitment continued until the start of the influenza season (December 4, 2016) for a total of 8 weeks. This recruitment period included a month of frequent Israeli national holidays (October 2016), during which enrollment was challenging because many HCP were on vacation. In Year 1 of the study, 596 HCP were enrolled, and will contribute to Years 1, 2 and 3 of this 3-year cohort study. Enrollment in Year 2 began in June 2017. New enrollees in Year 2 will contribute to Years 2 and 3 of the study.

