#### Sample size for immune response to vaccine and infection objectives

To assess the immune response to the vaccine, we plan to collect serum from the cohort members prior to vaccine availability, after vaccination, and at the end of each season. Our study design mirrors approaches used in previous studies that assessed the HI antibody titers among HCP analyzed sera from subgroups of 300–800 participants who provided sera at the same three time points [28]. See Additional file 1: Annex 7 for more details.

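### Compound symmetry forces equal variances on pre- and post-vaccination titers; if they differ, the GMT intervals are mis-sized, while the two-visit GMR interval stays correct with complete data

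*Protocol article*

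**What the plan says.** Under Data analysis of immunogenicity, the protocol article plans a linear mixed model for titers: "Pre- and post-vaccine draws are assumed to be correlated within each person, thus repeated measures linear mixed models will be fitted". The scale is fixed ("all statistical analyses will be conducted using log base-2 transformed titer data"), and so is the covariance: "Compound symmetric covariance error structures will be assumed for repeated measures within individuals".

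Both summary measures come from this model. For the level at a visit, "GMT will be calculated by back-transforming the least squares mean estimates of logged titer data". For the rise, "GMR will be calculated by back-transforming the difference of least squares means of post-vaccination and pre-vaccination logged titer estimates". When the section explains how covariates are chosen, it names the preseason GMT and the post-vaccination GMR as the outcomes of interest.

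Two other places bear on which draws might enter. The section on sample size for immune response says "we plan to collect serum from the cohort members prior to vaccine availability, after vaccination, and at the end of each season". Timeline of enrollment says of Year 1 that "596 HCP were enrolled, and will contribute to Years 1, 2 and 3 of this 3-year cohort study". Neither says that the end-of-season draw, or more than one season, goes into the mixed model. The article gives no SD or correlation for log titers.

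**The concern.** Compound symmetry has two parameters: one variance shared by all draws and one covariance shared by all pairs. With two draws, the restriction that matters is the equal variance.

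The study's own design gives reasons to doubt it. The two draws lie on either side of a vaccination meant to change the titer. Recruitment is stratified on prior-season vaccination, so baseline titers come from a deliberately mixed group. The assay section sets titers below 10 to 5, which compresses whichever draw has more low values. These are reasons why the variances might differ. They do not show that they do, and they need not all push in the same direction.

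At stake is the inference for objective 3, on repeated vaccination and immunogenicity. The preseason GMT is a single-visit quantity, so its interval depends directly on the common variance being right for that visit.

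**Working it through.** The article states no interval width, SD, correlation or power for this analysis, so there is no figure of its own to reproduce. All SDs and correlations below are assumptions on the log2 scale, shown as a range.

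**Two visits, complete data.** Let the true SDs be s1 and s2 and the covariance c. In large samples the compound-symmetry fit estimates the common variance as p² = (s1² + s2²)/2 and leaves c unchanged.

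- GMT at visit j: model SE / true SE = p / sj. Coverage of a nominal 95% interval = 2Φ(1.96 × ratio) − 1.
- GMR: model variance of the paired difference (per participant) = 2(p² − c) = s1² + s2² − 2c, which is the true variance. The ratio is 1 for any SDs and any correlation.

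Worked case, SDs 2.0 and 1.5:

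- p² = (4.00 + 2.25)/2 = 3.125, so p = 1.768.
- More variable draw: 1.768/2.0 = 0.884, coverage 91.7%.
- Less variable draw: 1.768/1.5 = 1.179, coverage 97.9%.
- GMR with correlation 0.5: c = 0.5 × 2.0 × 1.5 = 1.5. Model variance is 2(3.125 − 1.5) = 3.25 and true variance is 4.00 + 2.25 − 3.00 = 3.25.

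| Assumed SDs (larger / smaller) | SE ratio and coverage, more variable draw | SE ratio and coverage, less variable draw | GMR SE ratio |
|---|---|---|---|
| 1.5 / 1.5 | 1.000, 95.0% | 1.000, 95.0% | 1.000 |
| 1.8 / 1.5 | 0.920, 92.9% | 1.105, 97.0% | 1.000 |
| 2.0 / 1.5 | 0.884, 91.7% | 1.179, 97.9% | 1.000 |
| 2.0 / 1.0 | 0.791, 87.9% | 1.581, 99.8% | 1.000 |

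The table is the same whichever draw has the larger SD, and the GMR ratio was 1.000 at correlations 0.3, 0.5 and 0.7. If prior-vaccination groups share SDs of 2.0 and 1.5 and the preseason draw is the more variable one, a nominal 5% comparison of preseason GMTs rejects in about 100 − 91.7 = 8.3% of cases under no difference.

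**Simulation check.** A REML fit with a random participant intercept was used (300 participants, 150 runs per scenario, correlation 0.5, simulation error about 2 points). With pre and post SDs 2.0 and 1.5 and complete data, coverage was 91% for the pre GMT, 97% for the post GMT and 95% for the GMR, in line with the formulas. With 40% of post draws missing at random, GMR coverage was 99% for pre/post SDs 2.0/1.5, 95% for 1.5/2.0 and 94% for equal SDs. Missing post draws can therefore disturb the GMR interval, depending on the variances.

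**If a third draw were added.** The common variance v and covariance c then average over three visits, and the model variance of a contrast is 2(v − c). With equal SDs, only the correlations matter (order: pre-post, pre-end, post-end).

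- 0.5, 0.4, 0.8: mean 0.567. SE ratio for post/pre GMR = √[(1 − 0.567)/(1 − 0.5)] = 0.931, coverage 93.2%.
- 0.8, 0.5, 0.5: mean 0.6. SE ratio = √[(1 − 0.6)/(1 − 0.8)] = 1.414, coverage 99.4%.
- 0.5, 0.5, 0.5: ratio 1.000, coverage 95.0%.

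**The case against.** The strongest reply is that nothing in the article shows unequal variances. No SD is given, and the floor at 5 tends to compress low titers, typically those before vaccination, which could offset other influences and bring the two variances closer. This stands. A reader might infer that the intervals will have the wrong width; the documents support only that they will if the variances differ, and they do not say which draw would be affected in which direction.

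A reader might also infer that the GMR is at risk, because sera are taken three times per season and some participants stay for three seasons. The calculation can be made to look serious. With assumed SDs 2.0, 1.4 and 1.5 and correlations 0.5, 0.6 and 0.85, the model variance of any contrast is 2.15, against a true 3.16 for pre-to-post and 0.64 for post-to-end-of-season. But the analysis section names only pre- and post-vaccine draws and defines the GMR only between them. It does not define a post-to-end-of-season contrast, and no section says that seasons are pooled in this model. The objection succeeds here: these are conditional remarks, not findings about the stated model.

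Third, part of the remedy has limits. Once prior-vaccination group is a factor in the model, differences between group means leave the residual variance. If the groups differ in their covariances, one common unstructured matrix does not repair that.

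Finally, a missing fallback or assumption check may sit in the full protocol or the SAP, and its absence from an article is not a defect. That is right, but the covariance structure is not left open here. The article commits to it, so the choice can be assessed on its merits.

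**Conclusion.** The point holds in conditional form and is minor. The article commits to a structure that forces equal variances before and after vaccination. If they differ, GMT intervals, including those for the preseason GMT used for objective 3, are too narrow at the more variable draw and too wide at the other. For assumed SD ratios up to about 1.3 (2.0 against 1.5), coverage stays between about 92% and 98%; at a ratio of 2 it reaches 88% at the more variable draw. With equal variances there is no error.

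The pre-to-post GMR interval is correct for two complete visits. It becomes exposed only with missing post draws, or with added visits or seasons that the article does not place in the model. GMT and GMR point estimates from complete data are unchanged. The actual size in this study cannot be computed from the document.

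**What to change.** Replace compound symmetry with an unstructured within-season covariance for the log2 titers. Name heterogeneous compound symmetry or robust (sandwich) standard errors as the fallback if the fit does not converge. If seasons are pooled in one model, add a participant random effect to link them. State which draws enter the model.

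The cost is one or two sentences. The covariance parameters rise from two to three for two visits (one extra) and from two to six for three visits (four extra). The earlier studies that the article takes as its pattern used sera from 300–800 participants, which is ample for a 2×2 or 3×3 matrix. If compound symmetry is in fact true, almost nothing is lost.
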